#### Observational follow-up

Summaries of the outcomes measured in the observational follow-up will be produced using appropriate descriptive statistics. HbA1c at 30 months will be compared with the HbA1c estimates under intervention and control conditions in the RCT using mixed regression models accounting for repeated measures on the same patients and for the practice-level clustering. Similar analyses will be conducted for the secondary outcomes, including the process outcomes which will aid understanding about why changes are, or are not, sustained.

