## Background

Diabetes affects approximately 425 million people globally [1], with approximately 3.8 million in the United Kingdom (UK) [2], a figure that continues to rise [3]. It is estimated that by 2035, diabetes will account for 17% of National Health Service (NHS) expenditure [4]. Around 90% of people with diabetes have Type 2 Diabetes Mellitus (T2DM) [1], a serious, progressive, chronic disease, which leads to poor quality of life and increased prevalence of costly long term health complications. Despite advances in pharmacological interventions, management of T2DM remains a challenge.

Structured self-management education (SSME) for T2DM has been shown to be both beneficial and cost-effective [5–8]. Programmes such as DESMOND [6, 7], X-PERT [8] and the Diabetes Manual [9–11], have shown SSME to be associated with improved biomedical (e.g. HbA1c, lipids, weight, blood pressure), psychosocial (e.g. depression, quality of life, hypoglycaemia rates), behavioural, and medical outcomes [6–8, 12, 13]. A recent systematic review and network meta-analysis found that SSME on averaged reduced HbA1c by over 0.4%, with the greatest benefits seen in those with poor glycaemic control (HbA1c > 7.0%), aged less than 65 years and non-white participants [14]. Powerfully, another systematic review combining data from 42 trials, found a 26% reduced risk of all cause morality in those who had attended diabetes SSME compared to standard care [15].

Unfortunately, despite the increase in the quality and quantity of the evidence base since the National Institute for Clinical Excellence (NICE) first recommended SSME programmes and made SSME for T2DM a national priority in the UK [16], rates of uptake to SSME for those with T2DM have remained persistently low. The recent addition of a Quality and Outcomes Framework (QOF) indicator for referral to SSME in those with newly diagnosed T2DM [17] has improved the rate at which education is offered to people with newly diagnosed T2DM, with 74.5% of those with newly diagnosed diabetes (type 2 and other) being offered SSME within 12 months of diagnosis in 2016 as opposed to 47.4% in 2013 [18]. However, referral does not equate to uptake; moreover, many of these programmes may not be evidence based or meet the NICE criteria. The most recent national figures (2016) show that only 8.3% of T2DM patients were recorded as having attended SSME within 12 months of diagnosis [18].

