#### Observational follow-up design (months 18–30)

The 12-month observational follow-up is designed to investigate whether any improvements observed during the RCT are maintained. During this time the study team will no longer actively reinforce the Embedding Package, but practices can continue using the intervention provided during the RCT, if they choose to do so.

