### Primary and secondary outcome measures

All outcomes will be measured at baseline (0 month), first (0–9 months), and second (9–18 months) steps, as well as over the observational follow-up (18–30 months), except for the self-report data which will only be measured once by questionnaire (during the first step). All biomedical patient level outcomes will be extracted from primary care electronic medical records. For most of these outcomes, the last measurement within that time period will be used. For example, for the first step HbA1c will be defined as the last HbA1c measurement between months 0 and 9. If the variable has not been measured over that time period then it will be deemed missing.

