#### Primary outcome

The primary outcome is patient-level HbA1c compared between the control and intervention conditions in the RCT i.e. the baseline measure in the immediate group, and baseline and first step in wait-list group compared with first and second steps in immediate group and second step in wait-list group.

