### Randomisation

This is an open-label trial as it will not be possible to blind practices to their treatment arm. Practices will be randomised prior to baseline (month 0) in a 1:1 fashion to either: Immediate group (receive the Embedding Package for months 0–18), or wait-list group (provide usual care for months 0–9 then receive the Embedding Package for months 9–18). Randomisation will be stratified by CCG, and generated and implemented by a statistician. The statistician will provide the study team with the randomisation outcome so that they can inform practices of their allocation.

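### The 18–30 month HbA1c comparison has no concurrent usual-care practices, so it cannot tell a lasting benefit from change over time and should be reported as a before-after contrast

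*Protocol article*

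**What the plan says.** Sustainability is a secondary objective of the protocol article (Objectives). The 12-month phase after month 18 is "designed to investigate whether any improvements observed during the RCT are maintained" (Observational follow-up design). The analysis is stated under Analysis methods, Observational follow-up: "HbA1c at 30 months will be compared with the HbA1c estimates under intervention and control conditions in the RCT". The model named there is a mixed regression that allows for repeated values within patients and for clustering by practice.

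The two conditions are defined under Primary outcome: "the baseline measure in the immediate group, and baseline and first step in wait-list group compared with first and second steps in immediate group", with the wait-list group's second step also counted as intervention. Wait-list practices cross over at month 9 (Randomisation). In months 18–30, "During this time the study team will no longer actively reinforce the Embedding Package"; this holds for both groups, and practices may go on using the package if they wish.

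The article calls T2DM "a serious, progressive, chronic disease" (Background), says usual care may change over time (Control), and re-assesses eligibility at each step, so the cohort is open (Patients – data extraction and mail-out). It gives no expected rate of change in HbA1c and no precision for the follow-up comparison.

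**The concern.** The comparators for the follow-up value are all earlier in time. No practice is under usual care in months 18–30, so nothing shows what HbA1c would have been by then without the package. Progression of disease, changes in usual care, and turnover as newly diagnosed patients enter and others die or leave could each move mean HbA1c over one to two years. The target effect is only 0.1%, so modest movement is enough to decide the answer.

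At stake is the HbA1c part of the sustainability conclusion. Summary of study design says the phase is there to establish whether changes last, and the Discussion expects it to show longer-term improvement. The planned contrast could report a lasting benefit as lost, or a falling background trend as a lasting benefit.

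**Working it through.** **Inputs** (Sample size section unless stated): 29 practices per group, 460 patients per practice, SD 1.5%, ICC 0.05, target difference 0.1%. Two-sided alpha of 0.05 is assumed from the p-value threshold in Analysis methods. Measurement periods are month 0, months 0–9, 9–18 and 18–30 (Primary and secondary outcome measures).

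**1. Reproducing the plan's own figure.** The model has practice-period means, within-practice variance 2.25 × 0.95/460 = 0.00465, between-practice variance 2.25 × 0.05 = 0.1125, three periods with period effects, and sequences control-intervention-intervention and control-control-intervention. Generalised least squares gives SE 0.0219. The detectable difference at 80% power is (1.960 + 0.842) × 0.0219 = 0.061%, against 0.062% stated. The minimum cluster size is 171, against 174 stated. The stated design is therefore well approximated by this model.

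**2. How far back the comparators lie.** Window midpoints are 0, 4.5, 13.5 and 24 months; window ends are 0, 9, 18 and 30.

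- Control cells are month 0 in both groups and months 0–9 in the wait-list group. Simple mean gap: 24 − (0 + 0 + 4.5)/3 = 22.5 months at midpoints; 30 − (0 + 0 + 9)/3 = 27 months at ends. Weighted as the mixed model weights them, 1.91 and 2.29 years. The longest gap is 30 months (baseline to month 30); from the end of wait-list control to month 30 it is 21 months.
- Intervention cells: 24 − (4.5 + 13.5 + 13.5)/3 = 13.5 months; 30 − (9 + 18 + 18)/3 = 15 months. Model-weighted, 1.09 and 1.21 years.

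Staggered entry does not create an overlap. Practices were randomised from 06/08/2018 to 22/02/2019 (Recruitment). Taking month 0 as the randomisation date, the last control data fall by about 22/11/2019 and the first follow-up window opens about 06/02/2020.

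**3. Can a period term help?** With four period columns and two state columns (intervention, follow-up), the follow-up column equals the 18–30 month period column in both groups. The design matrix has rank 5 of 6. The follow-up effect is not estimable once period is in the model.

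**4. Size of the bias.** Suppose a true effect of −0.10% is fully sustained and no time term is fitted. Then

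follow-up minus control = −0.10 + drift × (1.91 to 2.29)

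follow-up minus intervention = drift × (1.09 to 1.21)

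The drift rates are assumptions; the documents give none.

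| Assumed drift (% HbA1c per year) | Follow-up minus control (truth −0.10) | Follow-up minus intervention (truth 0) |
|---|---|---|
| −0.05 | −0.20 to −0.21 | −0.05 to −0.06 |
| 0 | −0.10 | 0 |
| +0.02 | −0.06 to −0.05 | about +0.02 |
| +0.05 | −0.005 to +0.015 | +0.05 to +0.06 |
| +0.10 | +0.09 to +0.13 | +0.11 to +0.12 |

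The SE of follow-up minus control in this model is about 0.012, so a shift of 0.05 × 1.91 = 0.095 is about 8 SEs. Sampling error would not mask it.

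**5. The randomised contrast still available.** This is immediate versus wait-list at 18–30 months. The variance of a practice mean is 2.25 × (0.05 + 0.95/460) = 0.1171. The correlation with the baseline practice mean is 0.05/(0.05 + 0.95/460) = 0.960, assuming the practice effect is constant over time.

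- Baseline-adjusted: SE = √(2 × 0.1171 × (1 − 0.960²)/29) = 0.025; detectable difference at 80% power 0.070%.
- Unadjusted: SE = √(2 × 0.1171/29) = 0.090; detectable difference 0.25%.

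The adjusted figure is a best case, because a practice effect that drifts would lower the correlation.

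**The case against.** The strongest reply is that this limit comes with any wait-list design, that the phase is openly labelled observational and serves a secondary objective, and that sustainability does not rest on HbA1c alone. Process outcomes are to be analysed in the same way, ethnography runs to month 30, and the Discussion speaks of culture and practice as well as outcomes. All of that stands, and the process outcomes need no further request. The label does not remove the problem, because the article still fixes a model-based HbA1c comparison and describes the phase as showing whether changes last.

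A reader might infer four stronger points that the documents do not support.

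- *Progression will make a lasting benefit look lost.* The article calls the disease progressive but gives no HbA1c trend for this treated, open cohort. Evolving care and new diagnoses could offset or reverse a rise, so the sign is unknown.
- *Follow-up is judged only against control values.* Intervention-state estimates are also a comparator and bear most directly on maintenance. Their gap, and so their bias, is roughly half as large, but the confounding is the same.
- *The plan rejects the randomised contrast and season adjustment at follow-up.* The short section names neither. A full analysis plan is promised and not shown, so silence is not refusal.
- *The randomised contrast should be the main sustainability test.* It compares 18 with 9 months of delivery, with a package that may be changed at month 9 (Intervention). A null result fits both full maintenance and complete loss.

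**Conclusion.** The concern holds as a limit on interpretation that the protocol's wording does not respect. HbA1c at 18–30 months is compared with control values about 2 years older on average (up to 30 months) and with intervention values about 1.1–1.2 years older. Withdrawal of support cannot be separated from the passage of time, with or without a period term. Under assumed drifts of +0.05% and −0.05% per year, a fully sustained 0.1% benefit over control would appear wholly lost or doubled, and the comparison with intervention values would move by 0.05–0.06% either way. The drift rates are assumptions; the confounding follows from the design alone. This point concerns the follow-up phase only and leaves the primary 0–18 month result untouched. It should be corrected before the analysis.

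**What to change.** 1. In Analysis methods, Observational follow-up, call both HbA1c comparisons descriptive before-after contrasts, adjust them for season as in the primary model, and state that maintenance of HbA1c benefit versus usual care cannot be concluded from them.
2. Temper the matching statements in Summary of study design and in the Discussion.
3. Add one supplementary randomised analysis: HbA1c at 18–30 months, immediate versus wait-list, adjusted for CCG (the stratification factor) and baseline HbA1c, with practice clustering. Use the practice-level baseline mean, or patient-level values where they exist, since patients diagnosed after month 0 have none. State in advance that it estimates only the lasting effect of 18 versus 9 months of delivery, with a package that may differ after month 9, and that a null result shows neither maintenance nor loss.

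The cost is a few sentences and one extra model on data already to be extracted. The downside is a more modest sustainability claim for HbA1c.

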#### Integrated ethnographic study

Qualitative data will be analysed using the Framework Method [26]. Data will be coded and organised based on an established model for evaluating intervention design: Normalisation Process Theory (NPT) [27, 28]. Findings from the ethnographic work will be triangulated with quantitative data [29] to provide an in-depth and integrated explanation of the process of implementing the Embedding Package in a variety of contexts. The adoption of an inductive and reflexive approach will ensure rapid development and integration of findings from the earlier stages, and inform the optimisation of implementing the intervention, particularly in relation to sustainability.

#### Cost-effectiveness analysis

The general framework for the analysis is to describe the costs and effects of current levels of implementation using published estimates of the cost-effectiveness of patient education programmes, then estimate the incremental costs and benefits of increased implementation. These incremental costs and benefits will be a combination of the costs of the implementation activities, the associated increase in uptake and the cost effectiveness of the patient education programmes. This framework has been applied to implementation of QOF indicators [30] and is currently being developed further by the Department of Health Policy Research Unit for the Economic Evaluation of Health and Care Interventions (EEPRU).

The cost-effectiveness analysis will take an NHS perspective and model costs and effects over the lifetime of patients (with appropriate discounting). The costs of implementation activities will be generated from within the RCT. The Embedders will record all activity and the uptake of individual embedding activities in each provider will be recorded through an activity proforma, whilst unit costs for each activity will be generated via interviews in all providers across a sample of practices. The resources identified in each interview will be costed using either budget information from the practices/CCGs or external unit costs (e.g. Unit Costs of Health and Social Care). All other costs relating to diabetes care will be generated by the Sheffield T2DM policy model [31, 32] which will have its data sources updated through literature review and identification of the most recent unit costs.

The effects of the implementation activities will be measured in terms of quality adjusted life years (QALYs) estimated using the Sheffield T2DM policy model. The model will generate the QALYs via changes in HbA1c associated with SSME. Changes in HbA1c will be estimated in two ways. The primary analysis will be based on individual patient data from this RCT (as described above), whilst a secondary analysis will use published estimates of the effectiveness of SSME generated from a meta-analysis of RCT data. The central estimate of the incremental cost-effectiveness ratio of the Embedding Package will be presented, together with probabilistic estimates of cost-effectiveness represented in a cost-effectiveness acceptability curve. Value of information analysis will be undertaken using the Sheffield Accelerated Value of Information tool [33]. Deterministic sensitivity analysis will also be undertaken to explore the effects of uncertainties that cannot be adequately represented probabilistically; for example, the length of effect of the package, uptake rate without the package, and the mix of alternative education programmes to which patients are referred. Methods and results will be reported in line with Consolidated Health Economic Evaluation Reporting Standards (CHEERS) recommendations [34].

### Sample size

In the feasibility study an average cluster size of 460 was found across the six practices included (range 118–824) (Davies et al. Increasing uptake of self-management education programmes for type 2 diabetes in a multi-ethnic primary care setting: A feasibility study. 2019. In preparation). Recruiting 58 practices (29 to each randomisation point) will give over 90% power to detect a difference in HbA1c of 0.1% assuming an SD of 1.5%, based on United Kingdom Prospective Diabetes Study (UKPDS) [35]. There will be 80% power to detect a difference as small as 0.062%. This assumes an intra-cluster correlation coefficient (ICC) of 0.05, one baseline HbA1c measurement with one more HbA1c measurement at each randomisation point. This calculation does not take account of potential variation in cluster size, as methodological work has shown that the power of studies of a stepped wedge type design is robust to variation in cluster size [36]. The sensitivity of this calculation to changes in the average cluster size was assessed. As long as the average cluster size remains larger than 174 there will be 80% power to detect a 0.1% difference. To allow for potential cluster drop out of 10% the target will be to recruit 66 practices in total.

Return of a completed questionnaire booklet (self-report questionnaire and/or consent to link data form) will be recorded as consent to participate in the study. Additionally stakeholders and patients consenting to ethnographic interviews and observations will be recorded as participants. It is anticipated a minimum of 2050 participants will be recruited (2000 via questionnaire and 50 via interview/observation).

The integrated ethnographic study will be conducted within a sub-sample of approximately 12 of the practices and related contexts (e.g. CCGs and providers). Purposive sampling of practices will take place in the first and second steps of the RCT to ensure a representative sample [22]. A subset of 12 practices will provide data for the cost-effectiveness analysis.

### Dissemination

The team have a strong track record in generalising, disseminating and implementing research findings. Locally, results will be shared with primary and secondary healthcare organisations, public health bodies and local authorities. The community will be informed of key findings via a multimedia campaign using high profile public venues and services, local press, and accessible social media.. Local ethnic and cultural communities will be contacted through PPI groups and specialist local media.

Nationally, results will be submitted for publication in peer-reviewed journals and to the NIHR Library and for presentation at NHS, health policy, commissioning, diabetes and nursing conferences, to achieve wide dissemination to academic and clinical communities. The researchers will link with key NHS stakeholders (The Royal College of General Practitioners, the East Midlands Academic Health Science Network, The King’s Fund, the Strategic Clinical Network, the Health Foundation, the South Asian Health Foundation, and the NIHR, particularly Applied Research Centres, and Academic Health Science Networks) specifically with implementation in mind, holding regional events for NHS stakeholders. Findings appropriate to the general public will be disseminated through public organisations, national and local diabetes, third sector, the national Healthwatch network, and Diabetes UK. In consultation with PPI groups, we will take direction for prioritising methods of sharing key findings through popular media, through public information networks, and web-based technology. Evaluation of the impact of our communications strategy will be made through analysing the number of publications covering outcomes, web page hits and other success measures.

### Programme steering committee

A Data Monitoring Committee was not set up for this study given the low risk nature of the intervention, i.e. the intervention is aiming to increase uptake to established programmes which are recommended by NICE. An independent Programme Steering Committee has been appointed and agreed by the funders.

## Discussion

This mixed methods study will assess the effectiveness, cost-effectiveness and sustainability of the Embedding Package, an intervention which aims to improve biomedical and psychosocial outcomes of people with T2DM, through increased referral to and uptake of SSME. This study is timely. In 2017 the James Lind Alliance published the top ten research priorities in Diabetes, and the question “What is the best way to encourage people with type 2 diabetes, whoever they are and wherever they live, to self-manage their condition, and how should it be delivered?” was ranked third, highlighting the importance of this issue to patients with T2DM, carers, health-care professionals, and ethnic minority groups [37]. Given the high burden of disease and the current low levels of uptake to education, this study has the potential to have a big impact on the management of T2DM within the UK.

This trial is informed by a programme of work including development of the Embedding Package based on evidence from existing studies to identify experiential practices, procedures, strategies and plans which represent best practice. A feasibility study was then conducted which gave an opportunity to pilot the intervention and refine it based on ethnographic findings and to assess the feasibility of data collection processes. The results of the pre-trial studies are described in detail elsewhere (Davies et al. Increasing uptake of self-management education programmes for type 2 diabetes in a multi-ethnic primary care setting: A feasibility study. 2019. In preparation).

The trial not only assesses the effectiveness of the intervention but also includes an observational follow up phase. During this time no active trial input will happen, and the follow-up phase will therefore capture whether the Embedding Package can change culture and practice leading to longer term improvements. The trial is also pragmatic; all people with T2DM will be included irrespective of whether they are referred to or attend education during the study period. Therefore a small change in HbA1c is expected. In a study conducted at the patient level, a minimum difference of 0.3% in Hba1c may be clinically meaningful and lead to change in practice. Here the study is powered to detect a difference of at least 0.1%. This reflects the practice-level design of the study. Planned secondary analyses will try to elicit the effectiveness of the intervention in those referred to education during the course of the study. The study uses a wait-list design, similar to a stepped wedge design but with a single step during the study. The design is efficient as each practice acts as its own control and therefore produces a significant reduction in the sample size required compared to a standard cluster randomised trial. Given components of the intervention are delivered at the level of the CCG/providers, strategies to limit contamination of control state practices will be put in place during the first step.

If the Embedding Package is found to be both effective and cost-effective, a ‘toolkit’ to enable widespread implementation will be developed and rolled-out.

